### Interim analyses {21b}

Not applicable; no interim analyses are planned.

### Methods for additional analyses (e.g., subgroup analyses) {20b}

Not applicable; no subgroup analyses are planned.

### Methods in analysis to handle protocol non-adherence and any statistical methods to handle missing data {20c}

The statistical analysis is performed using the intention-to-treat population. To check the robustness of the effects, further analysis will be performed on the per-protocol collective. We will perform a sensitivity analysis to examine the effect of missing data in primary and secondary outcome variables. Missing data will not be replaced within this clinical trial.

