### Criteria for discontinuing or modifying allocated interventions {11b}

Patients can end participation in the trial at any time without any consequences for further care. They must be withdrawn from the trial when judged necessary by the investigator, as for safety concerns, severe non-compliance, incorrect inclusion, or new development of an exclusion criterion. The data that have been collected up to that time point will be included in the analysis.

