### Sample size {14}

The calculation of the sensitivity of the planned analyses is based on recent work, which investigated the effects of treatment with SAGE-271 (zuranolone) compared to placebo in patients with the depressive disorder [30]. We used least squares approximation to estimate the parameters of an Emax model [46] considering the scores of the HAMD-21 reported by Gunduz-Bruce and colleagues. This resulted in Emax TAU + PLC = 0.586 and ET50 TAU + PLC = 4.224. This means that comparable TAU with an additional placebo would lead to a reduction of the HAMD-21 scores of 58.6% and that half of this decrease would be reached after slightly more than four days.

Montecarlo simulations of an Emax model based on the mentioned parameter estimations for TAU and on the reported standard deviation of the HAMD-21 scores with s = 2.6 in the study of Gunduz-Bruce et al. [30] show that a sample size of 20 patients per group (TAU + placebo, TAU + etifoxine) is sufficient to detect chances of therapeutic efficacy (Emax) of about 5% and changes of the response latency (ET50) of about 10% with a statistical power of 70%. Assuming a drop-out rate of 10–20% we plan to recruit in total of 50 patients (25 per group).

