## Statistical methods

### Statistical methods for primary and secondary outcomes {20a}

Statistical analyses will be conducted by the Center for Clinical Studies, University of Regensburg in collaboration with the Biomedical Imaging group of the Department of Psychiatry and Psychotherapy, University of Regensburg. We will use SAS (version 9.4 or higher), Matlab (version 2021a or higher), R (R Core Team, 2020), and scikit-learn (1.3.2 or higher) for the analyses.

Baseline characteristics and demographic data will be presented descriptively for all patients and separately for the two treatment groups. Categorical variables will be reported by absolute and relative frequencies, interval scaled data using descriptive values like mean, standard deviation, median, interquartile range, minimum, and maximum.

Primary endpoint: Using the Nelder-Mead Simplex method (implemented in Matlab) we will conduct a nonlinear minimization of the square deviation of the HAMD-21 scores from an Emax function with the free parameters Emax and ET50 for each patient. Emax and ET50 will be tested each per t-test for mean value differences between TAU + Placebo and TAU + Etifoxine.

Secondary endpoints: All secondary endpoints will be analyzed only exploratory and will be defined in detail in the Statistical Analysis Plan. There will be no multiplicity adjustments of the *p*-values.

Safety endpoints: All data concerning the safety of the investigational product will be listed and reported in comparison to placebo. All (serious) adverse events will be summarized in frequency tables and will further be reported separatly according to intensity and relation to the investigational product.

Imaging data will be analyzed using specialized software (FSL, http://fsl.fmrib.ox.ac.uk) and with own Matlab- and Python-based programs. In all conducted tests we make no assumptions on the distribution of the data and therefore use computer-based randomization tests for the evaluation of significance.

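### Patients who leave before day 15 enter the primary t-test with an unstable ET50, or with none, because each curve is fitted alone and missing ratings are not replaced

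*Protocol article*

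**What the plan says.** Four statements in the protocol article act together.

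- **Population** (section {20c}): "The statistical analysis is performed using the intention-to-treat population". A per-protocol analysis is added as a robustness check.
- **Missing ratings** (section {20c}): "Missing data will not be replaced within this clinical trial". The same section promises, without naming a method: "We will perform a sensitivity analysis to examine the effect of missing data in primary and secondary outcome variables".
- **Withdrawn patients** (section {11b}): "The data that have been collected up to that time point will be included in the analysis". The withdrawal described there is from the trial, so ratings stop.
- **Primary analysis** (section {20a}): Nelder-Mead least squares of the HAMD-21 scores "from an Emax function with the free parameters Emax and ET50 for each patient", with no bounds stated. Then: "Emax and ET50 will be tested each per t-test for mean value differences between TAU + Placebo and TAU + Etifoxine".

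Ratings are scheduled at baseline, daily on days 1 to 8, and on days 15, 22 and 29. The primary objective looks at the period up to day 15, whereas section {18a} lists ratings up to day 29 for ET50. The sample size section allows for 10–20% drop-out.

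**The concern.** A two-parameter saturating curve can be located only if the ratings show both the initial slope and the approach to the plateau. A course that stops early shows mainly the slope. Many pairs of Emax and ET50 then fit almost equally well, and the fitted ET50 can land almost anywhere.

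The t-test on means ignores this. A value fitted to three ratings counts as much as one fitted to nine, and a mean is sensitive to a single extreme value. Patients with too few ratings cannot be scored at all, so the comparison would no longer contain everyone randomised although it is called intention to treat.

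At stake is the primary result: with 25 patients per arm, a few early leavers can move or blur the difference in mean ET50. If people leave because of non-response or side effects, the loss is also not random.

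**Working it through.** **Inputs from the sample size section:** Emax 0.586; ET50 4.224 days; SD 2.6; 20 evaluable patients per group; 10–20% drop-out; 50 randomised. The target is a 10% change in ET50, 0.10 × 4.224 = 0.42 days.

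**Assumptions not in the documents:** baseline HAMD-21 of 25; fractional reduction = Emax × t / (ET50 + t); SD 2.6 read as error per rating; scores scaled to the observed baseline rating. Where stated, between-patient variation is Emax SD 0.15 and ET50 coefficient of variation 40%.

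**1. The plan's own figure.** 20 / (1 − 0.20) = 25 per group, 50 in total. This reproduces. The allowance is 0.10 × 50 = 5 to 0.20 × 50 = 10 patients.

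**2. One post-baseline rating.** Let r be the reduction at time t. Then r = Emax × t / (ET50 + t) is solved by Emax = r × (ET50 + t) / t for any ET50 one chooses. There is no unique value, so the patient falls out or receives a number set by the starting point of the search.

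**3. Truncated courses, simulated.** Each simulated patient was fitted by Nelder-Mead from the plan's parameter values. The table shows the share with ET50 outside 1–15 days.

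| Last rating | With between-patient variation (500 per case) | Without it (range of three runs) |
|---|---|---|
| Day 15 | 28% | 23–25% |
| Day 8 | 39% | 37–42% |
| Day 5 | 61% | 60–62% |
| Day 3 | 77% | 76–79% |

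Simulation error with 500 patients is about √(0.39 × 0.61 / 500) = 0.022, or 2 percentage points.

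**4. Baseline treated as known** (400 per case, no between-patient variation).

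| Last rating | Interquartile range of ET50 (days) | Above 15 days | Negative |
|---|---|---|---|
| Day 15 | 2.7–7.5 | 7% | 1% |
| Day 8 | 1.8–9.9 | 17% | 2% |
| Day 5 | 1.3–62 | 34% | 5% |
| Day 3 | upper end diverges | 41% | 20% |

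The gradient does not depend on how the baseline rating is handled.

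**5. Leverage of one value.** With the noisy baseline, 17% of fits to day 8 and 28% of fits to day 5 exceeded 100 days, and some diverged beyond 1e14. A single ET50 of 100 in an arm of 25 moves the arm mean by (100 − 4.224) / 25 = 3.8 days, about nine times the 0.42-day target.

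**6. Does a change of rule help?** Imputing ratings to day 15 within arm and refitting brought early leavers to 29–31% outside 1–15 days, about the 28% seen in full courses.

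**The case against.** **A contradiction with the sample size?** A reader might infer that enlarging 20 to 25 per group conflicts with an intention-to-treat analysis. It does not. Inflating for drop-out and analysing everyone randomised is ordinary practice, and the sample size section does not say that drop-outs are removed. Keeping data up to withdrawal and not replacing the rest are also consistent with each other.

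**Are all 10–20% affected?** No. That figure is an allowance for all drop-out, and follow-up runs to day 29. Patients lost after day 15 keep the full course to day 15. Those lost between days 8 and 15 have eight daily ratings around the expected 4.2 days, so they lose precision rather than being read off beyond the data. The Discussion reports no drop-outs in the site's earlier etifoxine trials. This objection stands and limits the size of the point.

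**A fixed bias in days?** This is tempting but not supported. With 5/25 versus 2/25 drop-outs, the spurious arm difference is 0.12 times the shift in mean ET50. That shift depends on a bound which the protocol does not give. In one set of runs the difference was 0.02–0.08 days with a cap at 15 days, 0.14–0.42 at 30 and 0.41–1.27 at 60; a larger run at 30 gave 0.21–0.53. The median ET50 did not rise with truncation (3.9, 3.7, 3.3 and 2.7 days for courses ending on days 15, 8, 5 and 3).

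**Is drop-out the main cause?** Full courses to day 15 are already unstable in about a quarter of fits. This stands: imputation alone does not cure that.

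**Left to the analysis plan?** A rule for unfittable patients, the sensitivity method and the model for the day-15 HAMD-21 score may well be there, and none of these is counted here. But an analysis plan cannot impute ratings for the primary analysis without contradicting section {20c}, nor fit a joint model without departing from section {20a}. The sensitivity and per-protocol analyses do not repair the primary estimate, and a per-protocol set would tend to lose the same patients.

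**Conclusion.** The point holds in a limited form. The rules in sections {11b}, {20a} and {20c}, applied as written, give patients who leave before day 15 an unstable primary value at full weight, and give no unique value to a patient with one post-baseline rating. Under the stated assumptions, the share of fits outside 1–15 days rises from about 28% for courses to day 15 to 39%, 61% and 77% for courses ending on days 8, 5 and 3.

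The number of patients concerned is at most 5 to 10 of 50 and probably lower. The percentages rest on an assumed baseline, curve form and between-patient variation; the worsening with earlier exit appeared under every variant tried. No direction or size of bias in days should be quoted. The change is worth making because it needs only analysis and protects the primary comparison.

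**What to change.** In section {20c}, for the primary endpoint, replace the no-replacement rule by a method that uses every randomised patient's observed ratings under a stated missing-at-random assumption. Either of these would do:

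1. Multiply impute missing HAMD-21 ratings to day 15 within arm, using the daily ratings already taken. Fit the curves in each completed data set and pool the arm difference.
2. Fit one nonlinear mixed-effects Emax model to all observed ratings, with a treatment effect on ET50. This also changes section {20a}. It has the advantage of steadying the full-course fits, which imputation leaves as noisy as before.

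Use a delta-adjusted version, with drop-outs assumed worse than predicted, as the missing-data sensitivity analysis that section {20c} already promises. State the rating window for ET50 once, since the primary objective stops at day 15 and section {18a} runs to day 29.

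Cost: wording in the protocol and analysis plan and a little more analysis work, with no new patients or visits. The result will rest on the missing-at-random assumption, which the delta-adjusted analysis tests.

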### Plans to give access to the full protocol, participant-level data and statistical code {31c}

The full protocol as well as datasets used and/or analyzed during the current study can be made available by the corresponding author upon reasonable request.

## Oversight and monitoring

### Composition of the coordinating center and trial steering committee {5d}

This is a single-centre study and the coordinating centre of this study is the Department of Psychiatry and Psychotherapy of the University Regensburg. Two study assistants and two study coordinators (one medical investigator and one clinical psychologist) conduct local organization including the identification of potential recruits. Consent consultations are held by a medical investigator or a clinical psychologist of the study team. There are weekly meetings between the Principle Investigator, its deputy, the study assistants, and the study coordinators as well as PhD students whot are involved in the clinical trial. The whole study is closely monitored by the Centre for Clinical Studies of the University Hospital Regensburg. There is no Trial Steering Committee and no Stakeholder and Public Involvement Group for this randomized clinical trial.

### Composition of the data monitoring committee, its role and reporting structure {21a}

Data management is carried out by independent data managers of the Center for Clinical Studies, University of Regensburg. The primary check of the study data (source data comparison) is carried out by clinical monitoring. The completeness and plausibility of the recorded study data is checked by the data management using computer-aided and manual data checks. In the event of necessary data clarifications (queries), these are transmitted electronically to the monitor and the study center, where they are corrected or supplemented in the database.

### Adverse event reporting and harms {22}

Adverse events (AE) are recorded from the time the informed consent form is signed until the end of the clinical trial. At each study visit, the patient will be asked if there have been any health problems since the last visit. All AEs will be appropriately recorded, whether or not they are thought to be related to the investigational product. AEs are followed up for a maximum of 28 days after the end of trial participation until the symptoms have subsided, deviating laboratory values have returned to baseline values or, in the investigator’s opinion, no further findings are to be expected. This applies regardless of the causal relationship between the AE and the investigational product.

Incidents that meet the criteria of a serious adverse event (SAE) are reported by the ward staff to a medical member of the trial group. The latter immediately fills out an SAE form and forwards it to the investigator or his deputy. The investigator assesses a possible connection with the investigational medicinal product and makes a note of this. He forwards the SAE report form to the sponsor within 24 h of becoming aware of it.

If there is a suspicion of a causal relationship with the investigational product, the sponsor of the clinical trial is obliged to inform BfArM and the ethics committee. The maximum period is 15 days; in the event of a life-threatening or fatal case, the maximum period is reduced to 7 days.

### Frequency and plans for auditing trial conduct {23}

Monitoring will be performed by a monitor of the Center for Clinical Studies, University of Regensburg, which will regularly visit the center depending on the patient recruitment. It takes place according to a clinical monitoring plan. The study center was initiated by an initiation meeting in which the background of the study as well as the relevant procedures and measurements (e.g. getting informed consent, study medication, emergency unblinding) were presented. Regular visits will take place after every ten patients are included. For the first two patients, a 100% data comparison of the source date and the eCRF takes place.

### Plans for communicating important protocol amendments to relevant parties (e.g., trial participants, ethical committees) {25}

Any change to the study procedures defined as a substantial amendment according to the regulations of Good Clinical Practice must be made in written form, stating the reasons for the change. They must be signed by the investigator and his deputy as well as by the sponsor. They will be submitted to the ethics committee and the National Institute for Pharmaceutical Security (BfArM) and are only implemented after their approval. Changes in the technical conduct of the study that do not have a direct impact on the safety of study participants can be submitted to the ethics committee as a technical note. Administrative changes in responsibilities (outside actual patient care) can be reported to the ethics committee as an administrative change.

### Dissemination plans {31a}

We will publish the results of this clinical trial in international peer-reviewed journals and present them at national and international congresses. Both positive and negative results will be reported. We will further report the results in databases (EU Clinical Trials Register; German Register of Clinical Studies) and will create a lay summary for distribution to all participating patients. Within all publications, data protection is ensured for all patient-related data.

## Discussion

We here describe the study protocol for a single-center, randomized, placebo-controlled clinical trial on the effects of the TSPO ligand etifoxine in the treatment of depressive disorders. The primary objective of the trial is to investigate the effects of add-on treatment with etifoxine on clinical symptoms in patients with severe unipolar/bipolar depressive disorder. Clinical symptoms will be assessed using the HAMD-21 up to day 15 after the start of the treatment.

In advance, we were aware of some challenges in conducting this trial, including mainly the recruitment of eligible patients and their continuance in the study. We have taken several precautions to address these challenges as we pointed out in sections {15} and {18b}. Overall, we try to realize inclusion to the trial close in time to inpatient admission to increase the chance that included patients stay at the hospital until the end of the trial 29 days after starting the study medication. In any case, the primary outcome is measured at a relatively early time point (2 weeks after the start of the study treatment). Overall, the study team has a good track record in enrolling and following participants in previous trials and there were no drop-outs of participants in former trials investigating the effects of etifoxine at the site [47–49].

The merit of this study is that it is the first proof-of-concept study on the TSPO ligand etifoxine in the treatment of depression, which may promote endogenous neurosteroid synthesis. With its favorable side effects profile, it could become a valuable compound, which might help in enhancing the effects of established antidepressant medication as an alternative to exogenously administered neurosteroids, e.g., zuranolone*.*

## Trial status

The start of the recruitment was in April 2023. Currently (13th of January 2024), we included 15 patients. With a planned number of 50 patients, the recruitment and treatment period is estimated to be about a maximum of 33 months (until January 2026). The current protocol is version 4 of 7–7-2023.

## Data Availability

The datasets used and/or analyzed during the current study are available from the corresponding author on reasonable request.

## Abbreviations

AE: Adverse event
BDI: Beck-Depression-Inventory
BENDEP-SRQ: Benzodiazepine Dependence Self-Report Questionnaire
BfArM: *Bundesinstitut für Arzneimittel und Medizinprodukte* (National Institute for Pharmaceutical Security)
BHWSS: Benzodiazepine Hypnotics Withdrawal Symptom Scale
BOLD: Blood oxygenation level dependent
CANTAB: Cambridge Neuropsychological Test Automated Battery
CAR: Cortisol Awakening Response
Emax: Maximum effect which can be expected from a drug
ET50: Time point at which 50% of the maximal effect has occurred
FMRI: Functional magnetic resonance imaging
FNA: Face-name-associations
HAMD-21: Hamilton Depression Scale
IIT: Investigator-initiated trial
MADRS: Montgomery–Åsberg Depression Rating Scale
M.I.N.I.: Mini-International Neuropsychiatric Interview
PET: Positron emission tomography
PHQ-9: Patient Health Questionnaire 9
RSA: Representational similarity analysis
SAE: Serious adverse event
SSS: Stanford Sleepiness Scale
TAU: Treatment as usual
TSPO: Translocator protein
VAS: Visual analog scales
WOCBP: Women of Childbearing Potential
